## 16.3 Statistical analysis

### 16.3.1 General considerations

Statistical analysis is the responsibility of the CTRU Statisticians. The analysis plan outlined in Section 18.3 will be reviewed, and a detailed Statistical Analysis Plan (SAP) approved, before any formal analysis is undertaken. The SAP will be drafted in accordance with CTRU standard operating procedures (SOPs) and will be finalised and agreed by the trial and supervising statisticians, the Chief Investigator and other appropriate members of the research team. Any changes to the final approved SAP, and reasons for change, will be documented.

The proportion of missing data is anticipated to be non-trivial, making the handling of missing data an important issue for the analysis. Mechanisms for missing data on key variables will

be explored, with the proportion of missing data to be compared between intervention arms, and a multiple imputation model built covering the main analyses. As a sizeable proportion of patients are expected to be missing from the main analyses and the missing data predictable by known variables, the principal method for handling this will be multiple imputation under a Missing at Random (MAR) assumption. Sensitivity analyses will be carried out to assess the impact of the choice of imputation model and of assuming data are Missing Not at Random (MNAR), as appropriate.

As the primary clinical effectiveness analysis for each topic has a single primary outcome but two main treatment effects, 2-sided 2.5% significance levels will be used for these contrasts. Where results are subsequently combined when interpreting the treatment effect (e.g. across secondary outcomes), full consideration will be given to the family-wise error rate and further adjustments made for multiplicity, as appropriate.

Cluster randomisation of trusts/health boards rather than individual-randomisation of patients to interventions imposes recruitment-related clustering effects whereby patient outcomes are expected to be correlated. As the impact of cluster randomisation is expected to be equal across arms, the principal method for handling clustering will be to fit a multilevel model that constrains the cluster and patient level variances to be equal across arms, that is, a random intercept model. Sources of treatment-related clustering have been considered (e.g. provider and decision-maker) but there is only one provider (i.e. NCA) and it is not possible to collect linked data on the health professionals making transfusion decisions. As such, we recognise it as an unavoidable limitation that we will ignore this in the analysis.

Data distributions will be summarised, cluster and patient-level CONSORT diagrams will be generated and characteristics of clusters and patients at baseline and follow-up will also be summarised by intervention arm.

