## 16.2 Sample size

The sample size calculation has been refined following the grant application in light of decisions regarding the feedback interventions and transfusion topics. For each topic, there are two principal comparisons of interest (1. enhanced feedback documents vs. usual documents; and 2. Post-feedback support vs. no post-feedback support), relating to the two main effects of the 2X2 factorial design. Assuming that there will be 20% unnecessary transfusions at follow-up for each topic, that the ICC will be 0.05 and that cluster sizes will vary from 17 to 68 with a mean of 45, we need 152 clusters to detect a minimally important reduction of 6% (i.e. to 14% unnecessary transfusions) in the presence of, at most, a small antagonistic statistical interaction (i.e. 10% or fewer unnecessary transfusions in the enhanced feedback documents and post-feedback support) with 80% power using logistic regression models, with a random-intercept for cluster, and a 2-sided 2.5% significance level, for each comparison within each model. This requires us to recruit from England, Wales, Scotland and Northern Ireland and allows 12/171 (7%) clusters to be ineligible and 95% of those eligible to consent and be randomised. If these assumptions do not all hold, the tables below illustrate the impact on the minimally important clinical difference the trial would be powered to detect.

**Table 2: Sensitivity Analyses for ICC and recruitment assumptions fixing the power to detect the main effects at 80% & baseline proportion of unnecessary transfusions at 20%**

| ICC         | 150 Clusters   | 140 Clusters    | 130 Clusters    |
|-------------|----------------|-----------------|-----------------|
| 0.05 | (20, 14, 10.0) | (20, 13.5, 9.8) | (20, 13.0, 9.5) |
| 0.06 | (20, 13, 9.5)  | (20, 12.5, 9.3) | (20, 12.5, 8.9) |

|             |               |                 |                 |
|-------------|---------------|-----------------|-----------------|
| 0.07 | (20, 13, 9.0) | (20, 12.0, 8.8) | (20, 12.0, 8.4) |
| 0.08 | (20, 12, 8.5) | (20, 11.5, 8.3) | (20, 11.5, 7.9) |
| 0.09 | (20, 12, 8.0) | (20, 11.0, 7.8) | (20, 11.0, 7.4) |
| 0.10 | (20, 11, 7.8) | (20, 10.5, 7.5) | (20, 10.5, 7.0) |

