### **16.3.4 Primary endpoint analysis**

For each topic independently, the patient-level binary primary outcome of unnecessary transfusions 12 months following randomisation will be analysed using logistic regression, with a random intercept for trust/health board, adjusting for design factors (that is, trust size, regional transfusion committee, and trust-level proportion of unnecessary transfusions at baseline), with contrasts for (1) enhanced vs. standard documents, (2) post-feedback support vs. no post-feedback support, and (3) the interaction between (1) and (2).

Unadjusted and adjusted intra-cluster correlations (ICCs) and corresponding 95% confidence intervals will be presented. We will report the estimates and two-sided 97.5% confidence intervals for the two main effects from this model.

In addition to sensitivity analyses relating to assumptions about the missing data mechanism we will also analyse the supportive outcomes that include a grey-area category using ordinal logistic regressions and look for consistency in the size, direction and interpretation of effect.

Following the analysis of each topic independently, a further analysis will be conducted using data from both audit topics. This analysis uses a bivariate patient-level binary primary endpoint outcome of unnecessary transfusions 12 months following randomisation and will be analysed using multivariate logistic regression, with a random intercept for trust/health board and will be adjusted for the same design factors as above and additionally controlled for audit topic. The model will then include contrasts for (1) enhanced vs. standard documents, (2) post-feedback support vs. no post-feedback support and (3) the interaction between (1) and (2). We will then fit all possible interactions between (1), (2), (3) and audit topic; we do this in order to get unbiased estimators for the general effects of interventions accounting for possible interactive effects between the two trials on the intervention effects. Unadjusted and adjusted intra-cluster correlations (ICCs) and corresponding 95% confidence intervals will be presented. We will report the estimates and two-sided 97.5% confidence intervals for the two main effects from this model and also for the interactions between (1) and (2) and audit topic.

The same sensitivity analyses will be run on this model as with the separate models.

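### Testing each of the two main effects at a fixed 2.5% is valid, but Holm's step-down rule gives the same 5% family-wise error and more power when both interventions work

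*Protocol*

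**What the plan says.** Each trial has one primary outcome and two principal comparisons, which section 16.2 describes as "relating to the two main effects of the 2X2 factorial design". Three places in the protocol fix how they are tested:

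- Section 16.3.1 (General considerations): with "two main treatment effects, 2-sided 2.5% significance levels will be used for these contrasts".
- Section 16.2 (Sample size): 152 clusters give 80% power at a "2-sided 2.5% significance level, for each comparison within each model".
- Section 16.3.4 (Primary endpoint analysis): "We will report the estimates and two-sided 97.5% confidence intervals for the two main effects from this model".

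No step-down or other reuse of alpha is stated for these two contrasts. Section 16.3.1 goes on to mention family-wise error and further adjustment, but for results that are later combined, with secondary outcomes as the example. It does not change the rule for the primary contrasts.

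**The concern.** A fixed 2.5% on each contrast keeps the family-wise error within 5%, but it is not the most powerful simple way to do so. Under Holm, the smaller p-value is tested at 2.5% and, only if that is significant, the other at 5%. The family-wise error stays at or below 5% whatever the dependence between the tests, and no Bonferroni rejection is lost.

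What is at stake is a trial in which one main effect is significant at 2.5% and the other has p between 0.025 and 0.05. As written, the second is declared non-significant although 5% family-wise control does not require that. The primary objective (section 6.1) asks about both interventions, and the scenario behind the sample size has both of them working.

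There is also little room to gain power by adding clusters. Section 16.2 allows 12 of 171 clusters to be ineligible and 95% of the rest to consent: 159 × 0.95 = 151, which is about the target. Section 7 accepts as few as 130.

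**Working it through.** **Inputs from section 16.2.** Arm rates of 20%, 14%, 14% and 10%; "the ICC will be 0.05 and that cluster sizes will vary from 17 to 68 with a mean of 45"; 152 clusters; two-sided 2.5% per contrast; 80% power. The sample size section also gives 1,710 patients per arm.

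**1. Reproduce the stated 80%.** Take each main effect as the log odds ratio averaged over the other factor:

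- Effect = [(logit 0.20 − logit 0.14) + (logit 0.14 − logit 0.10)] / 2 = 0.405.
- Design effect = 1 + [(1 + CV²) × 45 − 1] × 0.05. The CV of cluster size is not given, so it is assumed from the range 17 to 68: 0.33 (uniform) gives 3.44, and 0.28 (range/4) gives 3.38.
- Standard errors are 0.1307 and 0.1296. Power = Φ(0.405/SE − 2.241) = 80.5% and 81.3%. Equal cluster sizes would give 83.5%.

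The protocol's 80% is reproduced. The correlation between the two contrasts is about 0.02, so near-independence is reasonable.

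**2. Power at each level, starting from exactly 80%.** Non-centrality = 2.241 + 0.842 = 3.083. Power at 2.5% = 0.800. Power at 5% = Φ(3.083 − 1.960) = 0.869. The difference is 0.069.

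**3. Both interventions work at the design size, contrasts independent.**

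| | Fixed 2.5% | Holm |
|---|---|---|
| Power per comparison | 80.0% | 0.800 + 0.069 × 0.800 = 85.5% |
| Power to show both | 0.800² = 64.0% | 0.869² − 0.069² = 75.1% |
| At least one rejection | 1 − 0.200² = 96.0% | 96.0% |

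The gain of 11.1 points in power to show both equals 2 × 0.800 × 0.0693: one p-value below 0.025 and the other between 0.025 and 0.05. A simulation of 2 million draws agreed (85.6% per comparison, 75.1% for both). With a correlation between the test statistics of +0.5 to −0.5, Holm power per comparison is 84.6% to 86.5%.

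**4. Only one intervention works.** Holm power for the real effect = 0.800 + 0.069 × 0.025 = 80.2%, against 80.0%. The chance of at least one rejection is 1 − 0.200 × 0.975 = 80.5% under both rules.

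**5. Family-wise error.** With no effect of either intervention and independent tests, it is 1 − 0.975² = 4.94% under both rules. With one true null, Holm's error on it is 0.025 + 0.025 × 0.800 = 4.5%, still below 5%.

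**The case against.** The strongest reply is that nothing here is wrong. The level is pre-specified, it is the same in the sample size, the test and the intervals, and it controls the error rate. That stands in full. A reader might infer from the power figures that the protocol's multiplicity control is faulty or that its 80% is misstated. Neither is so: the control is valid and the 80% is reproduced.

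The second reply is that the gain has a price. With 2.5% tests and 97.5% intervals, decision and interval always agree, and the two intervals jointly cover at 95% or more. Every extra rejection under Holm has p between 0.025 and 0.05, so its 97.5% interval always includes no effect. For independent contrasts, a 97.5% interval paired with a 95% interval covers jointly only 0.975 × 0.95 = 92.6%. This also stands. It matters because estimates of effectiveness feed the economic models (section 18.2). It calls for clear labelling, but does not outweigh the gain.

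The third reply is that the gain belongs to the favourable case. A reader might take Holm to be worth about 174 clusters instead of 152 (an information ratio of 1.147), or to repair a shortfall at 130 clusters, where power per comparison at the original effect would be 72.9% with the fixed level and 79.1% with Holm. Both figures need both interventions to work at full size, and section 7 itself records doubt that the effects are additive. The protocol also handles a shortfall differently, by holding power at 80% and tabulating the detectable difference. Nor does the comparison show that 152 clusters is the wrong number: to secure 80% for one intervention whatever the other does, Holm needs practically the same sample.

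**Conclusion.** The point holds as an inexpensive efficiency gain and not as an error. The fixed 2.5% level is valid but uniformly less powerful than Holm at the same 5% family-wise error.

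In the protocol's own scenario, the gain is 5.5 points of power per comparison and 11 points of power to show both effects. It rests on both interventions working at the design size, on main effects averaged over the other factor in a balanced 2×2, and on near-independent contrasts; moderate correlation changes the result by about one point. If one intervention has no effect the gain is 0.2 points, and the chance of at least one positive finding does not change in either case.

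**What to change.** Make these changes in the protocol, and carry them into the statistical analysis plan, before the single final analysis described in section 16.3.2:

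1. **Sections 16.3.1 and 16.3.4.** State that, for each topic, the two main effects are tested by Holm's procedure at a two-sided family-wise 5%: the smaller p-value at 2.5% and, if it is significant, the other at 5%.
2. **Section 16.2.** Keep 152 clusters. Describe 80% as the minimum power per comparison under the design assumptions, and reword the fixed level for each comparison to match.
3. **Section 16.3.4, combined analysis of both topics.** State whether the same rule applies. That model also reports 97.5% intervals for the two main effects and for their interactions with topic.
4. **Intervals.** Keep the 97.5% intervals as the simultaneous ones. Say in advance that a contrast declared only at the second step will have a 97.5% interval that includes no effect, and that its 95% interval will be shown beside it, labelled as not simultaneous.

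The cost is a few sentences in three sections, with no extra clusters or data. What is given up is exact agreement between test and simultaneous interval for a contrast declared at the second step.

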### **16.3.2 Frequency of analysis**

No interim analyses are planned. The two audit topics will be regarded as two trials, but with a single final analysis planned when all follow-up data from both topics has been databased, cleaned and locked. Screening and baseline data may be analysed separately.

### **16.3.3 Analysis populations**

The primary analyses will be carried out on an intention to treat basis, utilising all available follow-up data from all consecutive patients and imputing unavailable follow-up data, comparing allocated interventions. A complier average causal effect (CACE) analysis, comparing treatments received, will be considered if more than 10% of trusts or health boards do not implement the intervention as intended. This decision will be made without reference to the effectiveness data.

### **16.3.4 Primary endpoint analysis**

For each topic independently, the patient-level binary primary outcome of unnecessary transfusions 12 months following randomisation will be analysed using logistic regression, with a random intercept for trust/health board, adjusting for design factors (that is, trust size, regional transfusion committee, and trust-level proportion of unnecessary transfusions at baseline), with contrasts for (1) enhanced vs. standard documents, (2) post-feedback support vs. no post-feedback support, and (3) the interaction between (1) and (2).

Unadjusted and adjusted intra-cluster correlations (ICCs) and corresponding 95% confidence intervals will be presented. We will report the estimates and two-sided 97.5% confidence intervals for the two main effects from this model.

In addition to sensitivity analyses relating to assumptions about the missing data mechanism we will also analyse the supportive outcomes that include a grey-area category using ordinal logistic regressions and look for consistency in the size, direction and interpretation of effect.

Following the analysis of each topic independently, a further analysis will be conducted using data from both audit topics. This analysis uses a bivariate patient-level binary primary endpoint outcome of unnecessary transfusions 12 months following randomisation and will be analysed using multivariate logistic regression, with a random intercept for trust/health board and will be adjusted for the same design factors as above and additionally controlled for audit topic. The model will then include contrasts for (1) enhanced vs. standard documents, (2) post-feedback support vs. no post-feedback support and (3) the interaction between (1) and (2). We will then fit all possible interactions between (1), (2), (3) and audit topic; we do this in order to get unbiased estimators for the general effects of interventions accounting for possible interactive effects between the two trials on the intervention effects. Unadjusted and adjusted intra-cluster correlations (ICCs) and corresponding 95% confidence intervals will be presented. We will report the estimates and two-sided 97.5% confidence intervals for the two main effects from this model and also for the interactions between (1) and (2) and audit topic.

The same sensitivity analyses will be run on this model as with the separate models.

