For each trial, we initially adopted a 2X2 factorial design under the assumption of no statistical interaction in the effect of the two feedback interventions on patient and trust level outcomes. Once the nature of the two feedback interventions became clear, we questioned the likelihood of an additive effect. We gave detailed consideration to the impact of a range of plausible interaction effects on the statistical power available to detect both the main effects of interest and the interaction effect, which is of exploratory interest, and compared to three-arm design alternatives. We proceeded with a 2X2 factorial design because (i) the two comparisons of primary interest are those between each enhanced intervention and its usual comparator, and (ii) it may be argued that we were overly conservative in our initial estimate of the size of the clustering effect. As a consequence, the statistical power to detect the main effects remains fixed at 80% with minimal increases in the minimally important clinical differences that can be detected. The assumptions underlying the sample size calculation will be monitored throughout the project.

As part of the 2X2 design, all trusts and health boards in the UK will be invited to take part. NHS permissions will be sought and consenting clusters will be randomised to one of four interventions: usual documents, usual documents and post-feedback support, enhanced feedback documents, or enhanced feedback documents and post-feedback support following each baseline audit for the surgical and haematology patient audit trials respectively.

Outcomes will be obtained 12 months following each randomisation on an expected number of auditable cases of 45 per cluster but with an anticipated range from 17 to 68. While the target is still to randomise 152 clusters (6840 patients) for each topic, implications of randomising between 130 and 150 clusters have been considered; and the trial would still be

regarded as worthwhile if the target of 152 clusters proved impossible, but at least 130 clusters were included.

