**Note:** The first number in brackets (i.e. 20) is the proportion of unnecessary transfusions in the standard/standard arm. The second number is the largest proportion of unnecessary transfusions we could detect with 80% power in either the enhanced/standard or standard/enhanced arms. The last number is the largest proportion of unnecessary transfusions we could have in the enhanced/enhanced arm to be able to detect the main effects with 80% power. The power to detect the interaction ranges from 5% to 25% under these scenarios.

**Table 3: Sensitivity Analyses for ICC and recruitment assumptions fixing the power to detect the main effects at 80% & increasing the baseline proportion of unnecessary transfusions to 30% or 40%**

| ICC         | 150 Clusters     | 140 Clusters     | 130 Clusters     |
|-------------|------------------|------------------|------------------|
| 0.05 | (30, 23.0, 18.1) | (30, 22.5, 17.7) | (30, 22.0, 17.3) |
| 0.06 | (30, 22.5, 17.3) | (30, 22.0, 17.0) | (30, 21.5, 16.5) |
| 0.07 | (30, 22.0, 16.7) | (30, 21.5, 16.2) | (30, 21.0, 15.8) |
| 0.08 | (30, 21.5, 16.0) | (30, 21.0, 15.6) | (30, 20.5, 15.1) |
| 0.09 | (30, 21.0, 15.4) | (30, 20.5, 15.0) | (30, 20.0, 14.5) |
| 0.10 | (30, 20.5, 14.9) | (30, 20.0, 14.4) | (30, 19.5, 13.9) |
| ICC         | 150 Clusters     | 140 Clusters     | 130 Clusters     |
| 0.05 | (40, 32.0, 26.9) | (40, 31.5, 26.4) | (40, 31.0, 26.0) |
| 0.06 | (40, 31.5, 26.0) | (40, 31.0, 25.5) | (40, 30.5, 25.1) |
| 0.07 | (40, 31.0, 25.2) | (40, 30.5, 24.7) | (40, 30.0, 24.2) |
| 0.08 | (40, 30.5, 24.5) | (40, 30.0, 24.0) | (40, 29.5, 23.4) |
| 0.09 | (40, 30.0, 23.8) | (40, 29.5, 23.2) | (40, 29.0, 22.7) |
| 0.10 | (40, 29.5, 23.0) | (40, 29.0, 22.5) | (40, 28.5, 22.0) |

**Note:** The first number in brackets is the proportion of unnecessary transfusions in the standard/standard arm. The second number is the largest proportion of unnecessary transfusions we could detect with 80% power in either the enhanced/standard or standard/enhanced arms. The last number is the largest proportion of unnecessary transfusions we could have in the enhanced/enhanced arm to be able to detect the main effects with 80% power. The power to detect the interaction ranges from 4% to 9% under these scenarios.

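### Section 16.2 attaches 80% power to a single-intervention arm (20% to 14%); the design reaches 80% only for the main effect averaged over the other factor, and the single-arm comparison has about 60-65%

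*Protocol*

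**What the plan says.** Protocol section 16.2 gives the planning assumptions: "Assuming that there will be 20% unnecessary transfusions at follow-up for each topic, that the ICC will be 0.05", and "cluster sizes will vary from 17 to 68 with a mean of 45, we need 152 clusters". The effect to be detected is "a minimally important reduction of 6% (i.e. to 14% unnecessary transfusions", with "10% or fewer unnecessary transfusions in the enhanced feedback documents and post-feedback support", and it is to be found "with 80% power using logistic regression models, with a random-intercept for cluster, and a 2-sided 2.5% significance level, for each comparison within each model".

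The titles of Tables 2 and 3 fix the power for the main effects at 80%. The note under each table then says: "The second number is the largest proportion of unnecessary transfusions we could detect with 80% power in either the enhanced/standard or standard/enhanced arms". The same notes define the third figure by reference to the main effects.

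Section 7 describes "the interaction effect, which is of exploratory interest" and ties 80% power to the main effects. Section 16.3.4 puts documents, support and their interaction into one random-intercept logistic model as three contrasts. It adds: "We will report the estimates and two-sided 97.5% confidence intervals for the two main effects from this model".

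**The concern.** Two different quantities share the figure of 80%. One is the main effect of an intervention, averaged over the presence and absence of the other intervention, which uses all 152 clusters. The other is the effect of one intervention alone against usual/usual, which uses only half of them. The table notes and the named fall from 20% to 14% describe the second. The table titles and section 7 describe the first.

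A reader who takes the notes at their word would believe that the trial can confirm each intervention on its own against usual feedback with 80% power.

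The same ambiguity can carry into the analysis. In a model with an interaction, the coefficient called a main effect is an average under effect (plus/minus one half) coding and a single-arm effect under indicator coding. Section 16.3.4 does not say which is meant.

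**Working it through.** **Inputs from the protocol.** 38 clusters and 1710 patients per arm (152 and 6840 in all), mean cluster size 45, ICC 0.05, two-sided 2.5% (z = 2.241), rates 20% (usual/usual), 14% and 14% (one intervention), 10% (both).

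**Assumption.** The protocol gives a cluster-size range of 17 to 68 but no coefficient of variation (CV). I take 0 to 0.33; a uniform spread over that range has an SD of about 15, that is 15/45 = 0.33.

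**Design effect.** DE = 1 + ((1 + CV²) × 45 − 1) × 0.05.
- CV 0: DE = 1 + 44 × 0.05 = 3.20; effective n per arm = 1710/3.20 = 534.
- CV 0.25: DE = 3.34; effective n = 512.
- CV 0.33: DE = 3.445; effective n = 496.

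**Step 1: reproduce the stated 80%.** The margins are (20 + 14)/2 = 17% and (14 + 10)/2 = 12%, a main effect of 5 points. With 76 clusters a side at CV 0, the effective n is 1069 a side:
- SE = √((0.17×0.83 + 0.12×0.88)/1069) = 0.0152.
- 0.05/0.0152 = 3.29, and Φ(3.29 − 2.24) = 85%.

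Using the four cell variances instead, SE = √((0.16 + 0.1204 + 0.1204 + 0.09)/(4 × 534)) = 0.01515, and the power is 85.5%.

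On the log-odds scale, with the interaction kept and the effects averaged, the cell logits are −1.386, −1.815, −1.815 and −2.197:
- Averaged effect = ½(−0.429 − 0.382) = −0.405.
- SE = ½√(0.0117 + 2×0.0155 + 0.0208) = 0.126, and the power is 84%.

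**Step 2: the quantity named in the notes.** 20% against 14%, 38 against 38 clusters, CV 0:
- SE = √((0.16 + 0.1204)/534) = 0.0229.
- 0.06/0.0229 = 2.62, and Φ(2.62 − 2.24) = 65%.
- On log-odds: −0.429/0.165, and the power is 64%.

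**Results** (proportions by the pooled-variance formula / log-odds):

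| CV | Averaged main effect, 17% v 12% | Single arm, 20% v 14% |
|---|---|---|
| 0 | 85% / 84% | 64% / 64% |
| 0.25 | 83% / 82% | 62% / 62% |
| 0.33 | 82% / 80% | 61% / 60% |

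A beta-binomial simulation with cluster sizes uniform on 17 to 68 (20,000 runs) gave 79% and 60%.

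**Step 3: the rest of the tables.** On proportions at CV 0.33, all 54 cells of Tables 2 and 3 give 80-82% power for the averaged main effect. Single-arm power in the same cells is 60-79% in Table 2 and 60-69% in Table 3. The tables therefore reproduce as main-effect tables. The note comes closest to being true in the high-ICC cells of Table 2, where the assumed single-arm effect is largest.

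**Step 4: what a single-arm claim would need.** By the same proportions formula, 80% power for 20% against 14% in one arm needs about 212 clusters (CV 0) to 228 (CV 0.33). The averaged main effect needs about 134 to 144, so 152 is enough for it. With 152 clusters, a single arm could detect about 13.0% (CV 0) to 12.8% (CV 0.33) with 80% power, not 14%.

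**The case against.** The strongest reply is that the protocol means main effects throughout. Section 6.1 states the objectives as documents against usual documents and support against no support. Sections 7 and 16.2 tie the two comparisons to the main effects, and the table titles say the same. The third figure in each triple would be irrelevant to a single-arm comparison, so each triple can be read as a set of cell rates that yields 80% main-effect power. This stands as a guide to intent. It softens the mislabel but does not remove it, because one sentence in each note still gives a power that the design does not have.

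A reader might go further and infer that the confirmatory analysis loses about 20 points of power because the interaction is in the primary model. The protocol does not support that. The loss arises only under indicator coding, which section 16.3.4 never specifies; its talk of contrasts and main effects leans to the averaged reading. With effect coding the cost is slight: at CV 0.3, about 81% with the interaction kept and 82.5% without it. The coding may also be set in the SAP, which is not at hand.

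Single-arm power of 68% can be obtained by assuming a common variance on the logit scale. That assumption puts main-effect power at 90%, which does not match the stated 80%, so it should not set the top of the range. Likewise, reading 0.05 as a latent-scale ICC gives about 82% for the single arm but 96% for the main effect.

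Finally, at the planning rates the averaged and single-arm log-odds ratios are close (−0.405 and −0.429). The difference lies mainly in precision, not in the size of the effect.

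**Conclusion.** The point holds as an error of statement in section 16.2. The 80% belongs to the averaged main effect (17% against 12%, about 80-86% by formula). The comparison named in the text and the notes, 20% against 14% in a single arm, has about 60-65%.

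These figures rest on a cluster-size CV of 0 to 0.33, which the protocol does not give, and on an ICC on the proportion scale, which the tables support. They make no allowance for the planned covariate adjustment, including the trust-level baseline proportion.

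For section 16.3.4 the point is one of definition only. The primary contrasts should be pinned down so that an exploratory term cannot change what they estimate. Nothing shows that the planned analysis is underpowered, and the sample size of 152 clusters is not in question.

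**What to change.** 1. In section 16.2, say that 80% power refers to each main effect averaged over the other factor, 17% against 12% in the base case. Present 20/14/14/10% as the cell rates that produce it.
2. In the notes to Tables 2 and 3, describe the second figure as the assumed rate in the single-intervention arms under which the averaged main effect has 80% power. Add that the single-arm contrast against usual/usual has about 60-65% power in the base case, and state the cluster-size variation assumed.
3. In section 16.3.4, add one sentence: the two primary contrasts are averaged over the other factor, by effect coding or from a model without the interaction, and the interaction is exploratory. Carry the same definition into the SAP.

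The cost is a few sentences and the open statement of a less favourable figure for the single-arm contrast. No clusters, data, significance level or trial conduct change.
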